### Explanation for choice of comparator

Group 1 participants will be randomised to receive either a baseline (week 0) COVID-19 booster prior to commencing new or intensified immunosuppressive therapy and a DT booster at week 24 (Arm A) or a baseline DT booster and a week 24 COVID-19 booster (Arm B).

Participants in Group 2 will have undergone a BMT in the previous 9 months and received three post-BMT COVID-19 vaccines. These participants will be randomised to either receive their fourth post-BMT COVID-19 vaccine at baseline (week 0) (Arm C) or at week 24 (Arm D).

Due to the evolving nature of COVID-19 vaccine development, the study will accept any COVID-19 vaccine licensed for use in Australia. Due to established guidelines on post-BMT vaccination including diphtheria and tetanus, only COVID-19 boosters will be studied in Group 2.^16^

The DT vaccine was selected as the comparator for the COVID-19 vaccine. The DT vaccine is protein-based and stimulates an immune response via a different mechanism to that of currently available mRNA-based COVID-19 vaccines. The study will assess whether the findings that relate to the optimal timing of the COVID-19 booster also apply to more traditional protein-based vaccines. If this is found to be the case, then the study results may have broader implications for vaccinology and optimal clinical guidelines.

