### Outcomes

The primary outcome will be the integrated time-weighted area under the curve (AUC) anti-SARS-CoV-2 NAb response over 12 months from a SARS-CoV-2 booster as assessed by a high-throughput SARS-CoV-2 NAb platform assay developed by our group.^22^,^24^ The assay involves culturing a cell-line that is hyper-permissible to SARS-CoV-2 through the expression of ACE2 and transmembrane serine protease 2 receptors. Serial dilutions of patient serum are then introduced to the cell culture wells in addition to homogenous concentrations of SARS-CoV-2 virions including variants of concern. Anti-spike IgG present in the patient serum acts to block viral entry into the cell. The assay readout is the infectious dose 50% (ID_50_), the viral concentration required to obtain 50% cellular death.

Secondary outcomes include laboratory, safety and clinical/biological outcomes:

Laboratory outcomes:

NAb response to a tetanus toxoid booster integrated over 12 months.Responses to the COVID-19 vaccine includingBreadth of NAb against SARS-CoV-2 variants of concern.Kinetics of NAb over time including responses to variants of concern.Memory T cell, B cell and natural killer (NK) cell responses to peptide sets representing different domains of the SARS-CoV-2 spike protein.Immunological responses as assessed above in populations stratified by broad study-qualifying disease type and different modes of immunosuppression employed such as chemotherapy, BMT, B-cell depleting therapies and cytokine inhibition.

Safety outcomes:

Local and systemic AEs that occur in the 7 days following the DT and COVID-19 vaccinations.AEs following immunisation and adverse drug reactions following immunisation for the duration of the study.COVID-19 vaccine-induced disease flares.On-study PCR-confirmed or rapid antigen-confirmed SARS-CoV-2 infections.All on-study pregnancies.

Clinical/biological outcomes:

Health quality of life scores (EQ-5D-3L) at weeks 0, 24 and 48.Impact of immunosuppression on vaccine protection over time will be assessed by modelling:Level of protection over time based on NAb levels.Boosting and decay of anti-spike IgG, specific memory B, T and NK cell responses.Inform policies on the timing of additional COVID-19 boosters in vulnerable populations about to commence immunosuppression or following BMT.

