### Harms

All AEs occurring in the 7 days following booster vaccinations will be recorded on the electronic case report form (eCRF). Events will be MedDRA coded at data entry and details of their duration, severity, relatedness to the vaccination and management will be collected. All AEs and serious adverse events (SAEs) not related to participants’ underlying medical condition that qualified them for the trial, or to its treatment will be recorded on the eCRF. SAEs will be monitored continuously throughout the trial and will be recorded on both the eCRF and separately for onward reporting to the sponsor and ethics committee within 24 hours of an investigator becoming aware.

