### Randomisation

#### Sequence generation

Participants will be assigned to a study group based on their study-qualifying medical condition (table 1) using a central computer-generated randomisation sequence with a blocking factor of four created by the study statistician.

Participants in Group 1 will be stratified into one of two supra-stratum, haematological malignancy or systemic autoimmunity and then to sub-strata based on their planned treatment. Sub-strata include: haematological malignancy—chemotherapy; autoimmunity—B-cell depletion therapies; autoimmunity—anti-metabolite therapies; autoimmunity—TNFα-inhibition; autoimmunity—cyclophosphamide or alemtuzumab; autoimmunity—JAKi; autoimmunity—anti IL-17/23 monoclonal antibodies (table 1).

Group 1 participants will be randomised in a 1:1 ratio to receive either a COVID-19 booster at week 0 and a DT booster at week 24 (Arm A: immediate booster), or a DT booster at week 0 and a COVID-19 booster at week 24 (Arm B: deferred booster) (figure 1). Randomisation will be conducted using a central computer-generated random allocation algorithm using blocks and stratified by sub-strata population.

Group 2 has no sub-strata and participants will be randomised in a 1:1 ratio to receive either an immediate COVID-19 booster at week 0 (Arm C), or a deferred COVID-19 booster at week 24 (Arm D) (figure 1).

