#### Interim analyses

An interim safety analysis of full summary data examining booster vaccine-associated AEs, vaccine-induced disease flares and breakthrough COVID-19 infections will be performed when 30% (100) of participants reach the 24-week time point. A second safety analysis and an efficacy analysis examining the primary endpoint will be performed when 50% (160) of participants have reached 12 months. Additional meetings at which full interim data summaries will be reviewed may be scheduled following the occurrence of repeated or unresolved clinical events such that the Co-ordinating Principal Investigator (CPI) and DSMB Chair feel a full interim safety summary is warranted, or if the first DSMB meeting indicates a further meeting is warranted prior to all participants completing the study.

DSMB meeting reports will include open and closed session reports. Open session reports will include data on study conduct, protocol compliance, recruitment, baseline and follow-up characteristics and will be distributed to the PSC Chair, study statistician and DSMB members. Outcome results will not be discussed at open sessions. Closed session reports will be provided as unblinded reports and distributed only to DSMB members who will discuss outcome results, make decisions and formulate recommendations.

Following each DSMB review of full safety data, the DSMB will recommend to the PSC through the PI to (a) continue the study without modification, or (b) continue with stated modifications, or c) terminate the study.

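### The flare outcome covers only flares attributed to the COVID-19 vaccine, so the randomised DT control is lost for flares and a by-arm count can be confounded by disease stage

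*Protocol article*

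**What the plan says.** The safety list in the Outcomes section contains "COVID-19 vaccine-induced disease flares". DT is not named in that item, although another item in the same list names both vaccines: "Local and systemic AEs that occur in the 7 days following the DT and COVID-19 vaccinations". A further item, "AEs following immunisation and adverse drug reactions following immunisation for the duration of the study", is not limited to one vaccine.

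Under Sequence generation, Group 1 Arm A receives the COVID-19 booster at week 0 and DT at week 24, and Arm B receives them in the reverse order. Week 0 precedes new or intensified immunosuppression; week 24 falls about six months into it. Group 2 receives no DT. The Blinding section states that neither participants nor research staff can be blinded.

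The Harms section has all adverse events recorded for 7 days after a booster. Its general rule then covers adverse events and serious adverse events "not related to participants’ underlying medical condition that qualified them for the trial, or to its treatment will be recorded on the eCRF".

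The Interim analyses section gives the Data Safety Management Board (DSMB) "booster vaccine-associated AEs, vaccine-induced disease flares and breakthrough COVID-19 infections", with no vaccine named for the flares.

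**The concern.** Some flares of the qualifying disease will occur whatever vaccine is given. To tell a vaccine effect from that background, one needs the flare count in comparable participants, at the same stage of disease and treatment, who did not receive the COVID-19 vaccine at that time. Group 1 supplies such a group by randomisation: Arm B receives DT at week 0 when Arm A receives the COVID-19 booster, and the roles swap at week 24. An outcome restricted to flares attributed to the COVID-19 vaccine does not use it.

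If that outcome is tabulated by arm, Arm A contributes flares from the period around the start of therapy and Arm B contributes flares from the period after about six months of therapy. The two counts then differ in disease stage as well as in arm. The word induced also requires a causal judgement by people who know which vaccine was given, and without a parallel count after DT there is nothing to calibrate that judgement against.

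The DSMB reviews flares and may recommend modifying or terminating the study. A disease-stage difference could be read as an effect of vaccine timing, or a real effect could be hidden.

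**Working it through.** **The relevant sections side by side**

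- Outcomes: flares count if induced by the COVID-19 vaccine. DT is absent from this item but present in another item of the same list.
- Harms: within 7 days of either booster, all adverse events are recorded. After that, the rule covers events unrelated to the qualifying disease or its treatment. A flare is by nature related to the qualifying disease, so a flare on, say, day 20 after DT is covered neither by this rule nor by the flare outcome.
- Interim analyses: flares are vaccine-induced, vaccine unspecified.

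The difference between Outcomes and Interim analyses has a practical consequence. The first interim falls when 100 participants have reached week 24. Under the Outcomes wording, Arm A then has about 24 weeks of follow-up after its COVID-19 booster, while those Arm B participants just reaching week 24 have none. Under the Interim analyses wording, flares after DT could count, and both arms would contribute from week 0.

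**How large could a spurious difference be?**

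The protocol gives no flare rate, window, definition or flare analysis, so there is no figure of its own to reproduce. What follows is illustration under assumptions.

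Inputs:
- n = 280/2 = 140 per arm in Group 1 (Sample size section, 1:1 allocation).
- b0 = assumed background flare risk in a window after week 0.
- b24 = assumed background flare risk in an equal window after week 24.
- a = assumed share of background flares attributed to the COVID-19 vaccine, taken as the same in both arms.
- No true vaccine effect.

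The expected risk of a COVID-19-attributed flare is a·b0 in Arm A and a·b24 in Arm B, so the spurious excess is a·(b0 − b24). The chance of p<0.05 is the sum, over all pairs of counts (i, j), of Bin(i; 140, a·b0) × Bin(j; 140, a·b24) for which the two-sided Fisher exact p is below 0.05.

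With b0 = 15%, b24 = 5% and a = 1, the expected counts are 0.15 × 140 = 21 and 0.05 × 140 = 7, a risk ratio of 3.0. Fisher's test on 21/140 versus 7/140 gives p = 0.0086.

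| b0 | b24 | a | Spurious excess | Chance of p<0.05 |
|---|---|---|---|---|
| 10% | 5% | 1 | 5 points | 27% |
| 15% | 5% | 1 | 10 points | 76% |
| 20% | 5% | 1 | 15 points | 97% |
| 15% | 5% | 0.5 | 5 points | 37% |
| 15% | 5% | 0.2 | 2 points | 8% |
| 15% | 15% | 1 | 0 | 3% (the test's own error rate) |

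If b0 is below b24 the sign reverses. In the 240 participants with autoimmune disease alone (120 per arm), the 76% becomes 67%.

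**The concurrent contrast under the same assumptions**

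Counting all flares from week 0 in both arms, the expected counts at b0 = 15% are 21 (Arm A, COVID-19 booster) and 21 (Arm B, DT). The expected difference is zero at any background rate, because both arms are at the same disease stage.

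**The case against.** The strongest reply is that the protocol states no between-arm test of flares. Its arm comparisons are specified for immunogenicity endpoints, and safety tables and windows are commonly left to the analysis plan. That stands: this point criticises an outcome definition, not a stated test. But the definition itself is fixed here, and it determines which flares are available to tabulate.

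A second reply is that DT recipients are not ignored. Adverse events within 7 days of DT are recorded, adverse events following immunisation are collected throughout without restriction to one vaccine, and the interim wording names no vaccine. This also stands as far as it goes. A reader might infer that the DT arm is wholly unused for safety; the document does not support that. The gap is confined to the flare outcome and to disease-related events after day 7. The item on events following immunisation does not expressly lift the limit in the Harms section.

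A reader might also infer that immediate vaccination will appear harmful. That would require a higher background flare risk after week 0 than after week 24, and attribution of background flares to the vaccine. The first is plausible but nowhere stated. Nor is the contrast simply untreated against treated disease: some participants are intensifying existing therapy, concurrent corticosteroids are permitted, and the week 0 booster is given at most two weeks before therapy, so a longer window falls partly on treatment in both arms.

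Finally, the DT contrast exists only in Group 1.

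**Conclusion.** The point holds as a weakness in a stated outcome definition. The flare outcome is tied to one vaccine and to open-label causal attribution, the Group 1 arms receive that vaccine 24 weeks apart around the start of therapy, and the randomised concurrent DT control is lost for flares. The Outcomes and Interim analyses sections do not agree on which flares count, and the Harms section leaves disease-related events more than 7 days after DT without a clear route into the data.

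The consequence is that a by-arm count can be confounded by disease stage. Its direction and size cannot be known from the document. The figure of about 76% rests on assumed background risks of 15% and 5%, no vaccine effect, full attribution and 140 per arm; under the other assumptions shown, the chance runs from 8% to 97%, and there is no bias if background risks and attribution are equal. The primary antibody endpoint is unaffected. The change is worth making because it is cheap and uses arms and visits that the trial already has.

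**What to change.** - Define the outcome as any flare of the qualifying disease from randomisation onward, recorded in both arms under one definition, whatever the vaccine and whatever the attribution. Attribution may be kept as a secondary descriptor.
- In Group 1, compare arms as randomised within the same window: after week 0, COVID-19 booster (Arm A) against DT (Arm B); after week 24, DT (Arm A) against COVID-19 booster (Arm B). Stratify by sub-stratum.
- In Group 2, which has no DT, compare the immediate booster with no booster yet over weeks 0 to 24.
- Give the DSMB these contrasts rather than totals of COVID-19-attributed flares by arm.
- Reconcile the Outcomes, Harms and Interim analyses sections so that they agree on which flares count and are recorded.

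The cost is revised outcome wording, one flare question after the DT booster and new table shells. No extra visits are needed.

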## Abstract

**Introduction:**

Immunosuppression is associated with an increased risk of delayed SARS-CoV-2 viral clearance, severe COVID-19 and related death. This heterogeneous group of affected patients includes but is not limited to those with a haematological malignancy, people on immunosuppressive therapy for the treatment of autoimmune/inflammatory diseases and those following bone marrow transplantation (BMT). Immunosuppression is associated with decreased rates of anti-spike IgG seroconversion following COVID-19 vaccination. While clinical guidelines have been established to guide vaccination pre-splenectomy and post-BMT, there are limited data to guide timing of COVID-19 or other booster vaccines in adults commencing new or intensified moderate to severe immunosuppression. The comparison of immunity-boosting regimens for COVID-19 upon initiation of immunosuppressive therapy (CIRCUIT) study was designed to address this knowledge gap. CIRCUIT investigates whether administration of a third (or subsequent) COVID-19 booster vaccine ≤2 weeks prior to immunosuppression provides greater anti-spike IgG-mediated immunity than a booster given 24 weeks after new or intensified immunosuppression, that is, week 24 timepoint (Group 1; n=280). Additionally, the research will investigate whether giving a fourth post-BMT COVID-19 booster vaccine at 9 months post-transplant provides greater anti-spike IgG-mediated immunity than a booster given 15 months post-transplant (Group 2; n=40).

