## Introduction

### Background and rationale

 It was recognised early in the COVID-19 pandemic that immunocompromised individuals were at increased risk of severe disease,^1 2^ delayed viral clearance^3 4^ and death^5 6^ compared with the general population. Immunocompromised individuals comprise heterogenous groups including, but not limited to, those with solid organ and haematological malignancies, those with autoimmune and inflammatory disease on immunosuppressive therapies, allogenic and autologous bone marrow transplantation (BMT) recipients and solid organ transplant recipients. While these groups were prioritised in many COVID-19 vaccine programmes, evidence soon followed that vaccine seroconversion, including titres of anti-SARS-CoV-2 spike protein IgG were lower in immunocompromised individuals compared with healthy comparators. Patients with follicular lymphoma treated with immunochemotherapy had lower anti-spike IgG following two doses of BNT162b2 vaccine compared with those who were untreated and to healthy controls.^7^ Similarly, in patients with Waldenström Macroglobulinemia, those receiving Bruton’s tyrosine kinase inhibitors (BTKis) had lower anti-spike IgG following two doses of BNT162b2 vaccine compared with untreated counterparts and healthy controls.^7^ Studies of a third dose of COVID-19 vaccine in patients with haematological malignancies have demonstrated heterogeneous improvement in anti-spike IgG levels dependent on disease state and therapy. A retrospective observational study of 381 patients with haematological malignancies who received a third dose of a mRNA COVID-19 vaccine found detectable anti-spike IgG in 73.1% of patients after two vaccine doses which rose to 86.4% after three doses.^8^ Rates of seroconversion were lower in patients with chronic lymphocytic leukaemia (CLL) (52.6%) and B cell lymphoma (60.9%).^8^ While the third vaccine dose improved seroconversion for patients on Janus kinase inhibitors (JAKi) (from 57.1% to 90.9%), the rates of seroconversion remained low for patients with haematological malignancies on anti-CD20 treatment (55%), the bcl-2 inhibitor venetoclax (50%) and BTKis (37.5%).^8^ An additional study of 172 patients with CLL/small lymphocytic lymphoma (SLL) who did not seroconvert after two doses of a BNT162b2 vaccine received a third dose of the same vaccine.^9^ Overall, 23.8% of patients with CLL/SLL seroconverted following the third BNT162b2 vaccine with the highest rates among patients who were treatment naïve (40.6%) or off treatment (40%) while lower seroconversion was observed among those on active treatment (12%).^9^ Only one of 28 patients who had received an anti-CD20 B-cell depletion agent in the preceding year seroconverted (3.6%).^9^

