### Objectives

This study aims to evaluate the optimal timing of a COVID-19 booster vaccination in adults commencing moderate-to-severe immunosuppression for either an autoimmune/inflammatory disease or a haematological malignancy or who have undergone a bone marrow transplant in the previous 9 months. Efficacy will be assessed primarily by measuring the anti-SARS-CoV-2 neutralising antibody (NAb) response to the booster over 12 months. Other correlates of protective immunity as well as safety and quality of life will be assessed.

Delaying administration of the COVID-19 booster in the deferred arms may lead to higher numbers of breakthrough COVID-19 infections in these arms. The Data Safety Management Board (DSMB) will closely monitor on-study infections and advise the principal investigator and Protocol Steering Committee (PSC) should there be any concerns.

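### The infection outcome and the DSMB interim item name no severity, and the general AE/SAE recording left to catch serious COVID-19 has a treatment-related exclusion and is linked to neither

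*Protocol article*

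**What the plan says.** All references are to the protocol article.

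- **Why the population matters.** The Abstract's introduction links immunosuppression to an "increased risk of delayed SARS-CoV-2 viral clearance, severe COVID-19 and related death". Background and rationale repeats that "immunocompromised individuals were at increased risk of severe disease".
- **The harm foreseen from deferral.** Objectives states: "Delaying administration of the COVID-19 booster in the deferred arms may lead to higher numbers of breakthrough COVID-19 infections in these arms". The DSMB "will closely monitor on-study infections and advise the principal investigator" and the steering committee.
- **The safety outcomes.** Outcomes lists "On-study PCR-confirmed or rapid antigen-confirmed SARS-CoV-2 infections". The other safety items are reactions in the week after each vaccination, adverse events and reactions following immunisation over the study, vaccine-induced flares, and pregnancies.
- **The interim safety review.** Interim analyses names three items: adverse events associated with the booster, plus "vaccine-induced disease flares and breakthrough COVID-19 infections". The first review takes place when 100 participants reach week 24. A second safety analysis follows when 160 reach 12 months.
- **General event recording.** Under Harms, every adverse event in the 7 days after a booster is recorded. Beyond that, the events recorded are "All AEs and serious adverse events (SAEs) not related to participants’ underlying medical condition that qualified them for the trial, or to its treatment". SAEs are monitored continuously and sent to the sponsor and ethics committee within 24 hours.
- **Blinding.** Neither participants nor research staff are blinded.

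**The concern.** The trial deliberately delays a booster in half its participants and says openly that this may cost infections. Severe illness and death are what make those infections important in this population. Yet neither the outcome nor the interim item set up to watch for the harm names severity. Hospitalisation, oxygen or intensive care, and death from COVID-19 are not named anywhere as outcomes or as interim content.

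The severity of an infection then depends on the general AE/SAE record. Outside the post-vaccination week, that record has an exclusion which fits this event closely. A severe infection soon after starting strong immunosuppression is something a clinician could reasonably attribute to the immunosuppression. The person making that attribution knows the arm.

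At stake are the DSMB's ability to compare serious COVID-19 between arms while the trial runs, and the trial's ability to report the patient-important cost of waiting. Informing policy on booster timing is one of its listed aims.

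**Working it through.** The point rests on how the sections fit together, not on a figure in the plan. The check follows one case: a participant in a deferred arm is admitted to hospital with confirmed COVID-19 at, say, week 12, before the deferred booster.

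| Route | Does it register the case? | Does it register the severity? |
|---|---|---|
| Infection outcome (Outcomes) | Yes, with no condition on relatedness | Not named |
| Infection item (Interim analyses) | Yes | Not named |
| Booster-associated AEs (Interim analyses) | No; the COVID-19 booster has not been given | No |
| Vaccine-induced flares (Outcomes, Interim analyses) | No | No |
| All AEs within 7 days of a booster (Harms) | No; outside the window | No |
| General AE/SAE recording (Harms) | Only if judged unrelated to the disease and its treatment | Yes, if recorded |

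Steps:

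1. Only the last row can carry severity, and it is conditional. The exclusion is stated text: "or to its treatment will be recorded on the eCRF" closes a sentence confined to unrelated events.
2. The Harms sentence that promises details of severity directly follows the one on the 7-day window. Whether it reaches an infection months later is unclear.
3. Harms names the sponsor and the ethics committee as recipients of SAE reports. Neither Harms nor Interim analyses names SAEs or deaths as DSMB content.
4. Arm D is the clearest case. Group 2 receives no DT vaccine, so Arm D has no study-scheduled vaccination before week 24. During that window, the infection item is the only listed safety outcome that can register a COVID-19 harm.
5. For scale, the article gives no infection rate and no admission rate. The one usable input is the 1% mortality assumed under Sample size, which covers all causes:
   - whole trial: 0.01 × 320 = 3.2 deaths;
   - the 100 participants in the first safety review, over their whole follow-up: 0.01 × 100 = 1 death.
6. With about 3 deaths expected, one COVID-19 death attributed to immunosuppression would be 1 / 3.2 = 31% of the expected total. At such counts, a single case left off the record can change what the DSMB sees. No formal test would be informative, so listings by arm are the suitable display.

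**The case against.** The case on the other side is substantial, and part of it stands.

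- **A reader might infer that infections are only counted, or that a fatal case is weighed the same as a mild one.** The article does not say so. It names an event to capture and fixes no summary statistic and no weighting. That reading should not be adopted.
- **Serious cases would ordinarily be SAEs.** This is true under the usual definition, which the article does not print. SAEs are monitored continuously, and Data collection methods has coordinators review AEs and SAEs at every visit without repeating the exclusion. SAE records could also be matched to confirmed infections by participant. So it would be wrong to say that severe cases are invisible or that the trial could not report them. What remains is that the one sentence defining what is recorded does carry the exclusion.
- **A confirmed infection is recorded as an outcome whatever its judged cause.** This also stands. The exclusion threatens the record of the admission or death, not the record of the infection.
- **The outcome on adverse events following immunisation runs for the whole study.** Read widely, it could take in a later COVID-19 admission in Arm B, which receives DT at week 0. It cannot do so in Arm D before week 24, and the interim item is narrower because it is limited to booster-associated events.
- **The DSMB has wider powers.** The interim analysis is described as using full summaries, extra meetings are possible, and terms of reference were finalised before the study began. Those terms are not shown and may specify severity tables. But the article itemises what the interim analysis examines, and extra meetings depend on judgement, not on a planned comparison by arm.
- **A condensed article leaves detail elsewhere.** That is fair for eCRF fields and table layouts. It does not cover the exclusion, which is a printed rule, or the itemised content of the outcome and of the interim review.
- **Equal infection counts with unequal severity can be constructed.** Any such example needs invented rates, so none is relied on here.

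**Conclusion.** The point holds as a weakness in safety recording and monitoring. It does not touch the primary analysis. The infection outcome and the interim item name no severity, and the other interim items concern vaccination. Serious COVID-19 is left to a general record that excludes events attributed to the qualifying disease or its treatment. That attribution is made unblinded, and the record is not linked to the infection outcome or to the listed DSMB content. Followed as written, these rules allow a COVID-19 admission or death to be left off the SAE record, and they put no severe COVID-19 item into the planned review of the harm that the article itself foresees.

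The size cannot be estimated from the article. Severe cases would be few: about 3 deaths from any cause are expected in the whole trial.

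The conclusion assumes that the Harms text reflects the rule sites follow, that SAE has its usual meaning, and that the DSMB guidelines and full protocol, which are not shown, do not already lift the exclusion or supply the link. If they do, the remaining step is to align the article with them. The change is worth making because it is specific and cheap.

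**What to change.** 1. **Harms:** state that the exclusion for events related to the qualifying disease or its treatment does not apply to confirmed SARS-CoV-2 infection or its complications.
2. **Outcomes:** for each confirmed infection, record hospitalisation, oxygen or intensive care, and death, whatever the judged cause.
3. **Interim analyses and final report:** show these by randomised arm as listings and simple counts, with no formal test. Present Group 2 separately, as Statistical methods already does.

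The cost is a few eCRF fields completed at existing visits and one extra DSMB table. The downside is a small data-entry load and events too few for inference, so the table informs the DSMB's judgement and does not support a claim about effect.
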